**Ethics and dissemination:**

The study has been approved by the ethics committees of the Department of Anthropology, University of Delhi and Sardar Patel Medical College, Rajasthan. We are taking written informed consent after discussing the various aspects of the study with the participants in the local language.

Strength and limitations of this studyThis is a longitudinal study in India to examine trimester-specific metabolomic changes during the course of pregnancy and their influence on fetal growth.The study is collecting biological measurements on pregnant women during each trimester (first, second and third trimester) and their offspring at the time of birth.Newborns will be intensively phenotyped for the levels of metabolites and body composition.Unlike other Indian cohorts, the study participants are being recruited from a government hospital that caters for a rural population.Lack of information on prepregnancy measurements will restrict our analysis to the duration of pregnancy only.

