### Relationships between maternal gestational weight gain and newborn health

Gestational weight gain (GWG) is a complex biological trait which is influenced by maternal physiology, maternal, placental and fetal metabolism.^28^ There are short-term or long-term implications of inadequate or excessive GWG which direct the trade-off between maternal and child health outcomes.^28–32^ For example, inadequate weight gain is associated with high risks of low birth weight, small for gestational age and preterm birth.^33^ Excessive GWG is associated with large for gestational age, gestational diabetes, caesarean section and postpartum weight retention.^34^ Furthermore, high prepregnancy maternal body mass index (BMI) is associated with perturbations to maternal metabolome across gestation.^35^

Maternal GWG is a good indicator of fetal nutrition.^36^ Any amount of weight gain in the first 14 weeks and high rate of weight gain (>500 g/week) in 14–36 weeks are associated with raised adiposity in the offspring.^37^ GWG in the first trimester is associated with offspring BMI from infancy to early childhood whereas excessive GWG (ie, ≥500 g/week) in second and third trimesters is associated with increased birth weight.^38^ In the first half of the pregnancy (<20 weeks), excessive GWG is associated with higher birth weight and high body fat in newborns compared with the second half of pregnancy.^39^ Furthermore, Gaillard *et al*

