### Study objectives

To detect differential changes in quantitative metabolites between the end of the first, second and third trimesters of pregnancy and to examine how these trajectories are associated with maternal weight gain.To determine the influence of metabolic changes during pregnancy on fetal growth, body composition (fat mass, lean mass and bone density) and anthropometry at birth (ie, body length, weight and circumferences) independent of maternal prepregnancy BMI and paternal phenotypic characteristics.To assess the association between maternal metabolic profile during pregnancy and metabolite levels of offspring at birth (in cord blood).

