### Questionnaires

A comprehensive questionnaire has been developed for collecting information on demographic, anthropological (caste, religion and consanguinity), medical disease history, tobacco and alcohol intake and passive smoking. The validated food frequency questionnaire of '*Indian Migration Study'* is being used for evaluating dietary intake.^79^ Maternal physical activity during pregnancy is being assessed using the international physical activity questionnaire (ie, 7 days long).^80–82^ The assets-based tool of National Family Health Survey-4 is being used to evaluate socioeconomic position.^83^ For assessing depression, we are using the Patient Health Questionnaire^84^ and Edinburgh Postnatal Depression scale.^85^ The WHO-5 questionnaire is being used for collecting information on quality of life.^86^ The capability well-being, that is, individual’s freedom to function in five key areas of their life: ’stability', ’attachment', ’achievement', ’autonomy' and ’enjoyment', is being assessed by using the ICEpop CAPability measure for Adults.^87–89^ Information on maternal environment, gynaecological and obstetrics history is also being collected using tools adapted from INTERGROWTH study.^90 91^ Additionally, a structured questionnaire on social factors like relationships with family members, husband position in household, social support during pregnancy and travel is being used for assessing the quality of social life and adequacy of social support (table 1).

**Table 1 T1:** Measures, tools and time points of data collection

	Mother			Offspring
	First trimester	Second trimester	Third trimester	
Timing of data collection	10th to 13th weeks	22nd to 24th weeks	32nd to 34th weeks	Birth
Gynaecological and obstetric	✔	✔	✔	–
Socioeconomic position	✔	✔	✔	–
Anthropological (caste and religion)	✔	✔	✔	–
Education	✔	✔	✔	–
Marital status	✔	✔	✔	–
Smoking	✔	✔	✔	–
Alcohol drinking	✔	✔	✔	–
Medication	✔	✔	✔	–
Disease history	✔	✔	✔	–
Maternal environment	✔	✔	✔	–
Physical activity (IPAQ)	✔	✔	✔	–
Time-activity pattern	✔	✔	✔	–
Food frequency	✔	✔	✔	–
Dietary recall (3 days)	✔	✔	✔	–
PHQ-12	✔	✔	✔	–
Well-being (WHO-5)	✔	✔	✔	–
Depression (EPNDS)	✔	✔	✔	–
Social factors	✔	✔	✔	–
Capability well-being (ICECAP-A)	✔	✔	✔	–
Anthropometry				
Height/body length	✔	✔	✔	✔
Sitting height	✔	✔	✔	–
Weight	✔	✔	✔	✔
Circumferences	✔	✔	✔	✔
Skinfolds	✔	✔	✔	✔
Blood pressure	✔	✔	✔	–
Laboratory tests: Glucose, insulin, Hb, lipids, LFT and KFT and blood group	✔	✔	✔	✔
Metabolomic data	✔	✔	✔	✔

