### Adult anthropometry

The assessment of anthropometric traits (weight, height, sitting height, circumferences and skinfolds) are being performed on study participants using standard procedures.^92^

Weight is being measured when the participant standing straight on the centre of the weighing machine (Tanita, model-HD380), arms hanging freely with minimum clothes and without accessories. Height is being measured as the vertical distance between vertex (highest point on head) and floor when the participant standing straight with feet together on the level floor without footwear, arms resting by the side, with head in eye-ear plane (Frankfort horizontal plane) and heels, buttocks and shoulders projected on the vertical plane using a wall-mounted stadiometer (ADE, Germany, model-MZ10023-3). Sitting height is being measured as the maximum distance from the vertex (top of the head) to the base of a flat sitting surface, with legs hanging freely and head in eye-ear plane.

Circumferences are being measured at the specific landmarks when the plane of the tape (ADE, model-MZ10021) is perpendicular to the long axis of the body and parallel to the floor without tape being pulled too loose or too tight. Waist circumference is being measured at the narrowest point (which is an approximate midpoint) around the waist between the lower rib margin of the last palpable rib and the top of the iliac crest with the help of a measuring tape. Mid-upper arm circumference is being measured at the midpoint between the tip of the shoulder and the tip of the elbow (acromion and olecranon process, respectively) taken horizontally (at the middle of the biceps). Hip circumference is being measured at the widest part of the hip (buttock) at the level of the trochanterion, which is the most superior point on the greater trochanter of the femur, not the most lateral point. Calf circumference is being measured on the right leg as the maximum circumference in a plane perpendicular to the long axis of the calf until the greatest circumference is located when foot is placed on raised platform.

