### Data analyses

The evaluation of cross-sectional associations of maternal body weight with quantitative metabolite levels in each trimester, independently, will be done using regression-based modelling. Both level of metabolites and gestational weight in each trimester will act as exposure as well as outcome. Variables like socioeconomic position, gestational age, parity, diet, smoking and physical activity will be considered as confounders. Maternal characteristics will be considered as exposures (like trimester-specific weight, metabolite levels) to evaluate their association with offspring-related outcomes (fetal growth, birth weight, body compositions and metabolite levels). The potential confounders for maternal-offspring associations will be socioeconomic position, gestational age, parity, diet, sex of the offspring, smoking and physical activity.

Mixed effects regression models for repeated measures will be applied for examining longitudinal associations of weight gain from first to third trimester^42^ with maternal levels of metabolites during pregnancy and fetal growth.^105^ We will also analyse the associations of level of metabolites from first to third trimester with trajectories of GWG. Mediation analyses will be conducted for evaluating the role of maternal metabolites as intermediates between GWG and offspring’s body composition.^106^ False discovery rate based multiple testing correction for number of metabolites will be applied.^107^ Mediation analysis will be conducted to examine whether the effect of GWG on fetal growth is mediated through alteration in levels of circulating metabolites.

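### Objective 2 claims independence from prepregnancy BMI and paternal phenotype, but the article has no prepregnancy data, describes no paternal measurement, and names no maternal size covariate for the mother-to-offspring models

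*Protocol article*

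**What the plan says.** Under Study objectives, the second objective is to determine how metabolic changes in pregnancy influence fetal growth and the newborn's composition and size, "independent of maternal prepregnancy BMI and paternal phenotypic characteristics".

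The strengths and limitations list, printed with the abstract's Ethics and dissemination paragraph, states: "Lack of information on prepregnancy measurements will restrict our analysis to the duration of pregnancy only". Table 1 (Questionnaires) puts the first maternal visit at the "10th to 13th weeks". At the trimester visits, according to Adult anthropometry, "The assessment of anthropometric traits (weight, height, sitting height, circumferences and skinfolds) are being performed on study participants".

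Table 1 has columns for mother and offspring only. The one item on the father that the article names is a social one: "husband position in household".

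Data analyses gives two confounder lists. For maternal weight and metabolites: "Variables like socioeconomic position, gestational age, parity, diet, smoking and physical activity will be considered as confounders". For the associations that Objective 2 concerns: "The potential confounders for maternal-offspring associations will be socioeconomic position, gestational age, parity, diet, sex of the offspring, smoking and physical activity". In the offspring analyses, trimester-specific maternal weight is named as an exposure.

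The Introduction says that "high prepregnancy maternal body mass index (BMI) is associated with perturbations to maternal metabolome across gestation". Its section on maternal metabolic associations with newborn phenotypes reports 55 g higher birth weight per SD of genetically elevated prepregnancy BMI, from a Mendelian randomisation study.

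**The concern.** A result can be called independent of a variable only if that variable, or a declared stand-in, enters the design or the model. Here one of the two named variables is disclaimed elsewhere in the same article. The other has no described source. The model that should deliver the objective lists neither, and it lists no other measure of the mother's size.

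On the authors' own account, prepregnancy BMI is associated with the exposure (maternal metabolites) and with an outcome (birth weight). Leaving maternal size out therefore opens a path by which a metabolite with no effect of its own can appear to predict newborn size. The report could then claim an independence that was never examined, although height and weight are measured on every woman at the first visit.

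**Working it through.** **1. The objective set against the rest of the article**

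- *Prepregnancy BMI.* Promised in Study objectives; declared unavailable in the limitations. The earliest weight is at 10–13 weeks, and the text does not name BMI at that visit as a proxy.
- *Paternal phenotype.* Promised in Study objectives. Table 1 has no paternal column or row, the assessment sections describe no measurement of fathers, and Data capture, protection and management assigns identification numbers to mothers and newborns only.
- *The model.* The mother-to-offspring list has seven variables. None is BMI, weight or height, and none is paternal. Maternal weight enters as an exposure or outcome.

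This comparison alone supports the main point. The arithmetic below only asks how large the resulting bias might be.

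**2. The plan's own figure for this objective**

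Sample size states 80% power for R² = 2% of fetal growth, N = 1000, α = 0.0001. By Fisher's z:

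- atanh(√0.02) × √997 = 0.1424 × 31.58 = 4.50
- two-sided: Φ(4.50 − 3.89) ≈ 72.7% (noncentral F: 72.9%)
- one-sided: Φ(4.50 − 3.72) ≈ 78.1% (noncentral F: 78.3%)

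The stated 80% is met to within about 2 points only as a one-sided figure. Nothing in this point depends on it; the 2% serves only as a yardstick.

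**3. Bias from omitting BMI**

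If a metabolite has no effect and BMI drives both variables, the induced correlation is

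r(induced) = r(BMI, metabolite) × r(BMI, birth weight).

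Inputs:

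- from the document: 55 g per SD of BMI
- assumed: birth-weight SD 400–500 g, so r(BMI, birth weight) = 55/500 to 55/400 = 0.11 to 0.1375
- assumed: r(BMI, metabolite) = 0.1 to 0.5

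Results at N = 1000 (rejection rates by noncentral F with λ = N·R²/(1 − R²)):

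| | Low end | High end |
|---|---|---|
| Induced r | 0.1 × 0.11 = 0.011 | 0.5 × 0.1375 = 0.069 |
| Induced R² | 0.01% | 0.47% |
| Rejection rate at α = 0.0001 | 0.02% | 4.3% |

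With larger assumed BMI–birth weight correlations of 0.2–0.3 and BMI–metabolite correlations of 0.2–0.5, the induced R² runs from 0.04² = 0.16% to 0.15² = 2.25%. Only the top of that range reaches the 2% yardstick.

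**4. Two limits of the illustration**

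- Data analyses plans false discovery rate control, not a fixed 0.0001, so the per-test cut-off could be looser. If, for example, 40 of 400 metabolites were declared at an assumed 5% rate, the cut-off would be 0.05 × 40/400 = 0.005. A null metabolite with induced r = 0.069 (z ≈ 0.069 × √1000 = 2.2) would pass it about a quarter of the time.
- Objective 2 concerns metabolic *changes*, whereas the calculation uses metabolite *levels*. The document gives no figure for how BMI relates to within-woman change.

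**The case against.** The best defence is that this is a condensed article, and the full covariate set belongs in an analysis plan that is not shown. The weight–metabolite list is illustrative, the mother-to-offspring list is headed as potential confounders, and neither says that nothing else will enter. Objective 2 itself signals an intention to account for BMI. The lack of prepregnancy data is openly disclosed, and height and weight at 10–13 weeks allow a repair at the analysis stage.

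Much of this stands, and it limits the point in four ways.

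- A reader might infer that no model in the study will adjust for maternal size. The documents do not support that: the weight–metabolite list is open-ended, and Objectives 1 and 3 make no claim of independence. The omission of maternal age is likewise a detail that can be left to an analysis plan.
- A reader might infer that fathers are not measured. The article never says so. Its general questionnaire is not itemised and Figure 2 is not shown. The accurate statement is that no paternal measurement is described.
- A reader might infer that the estimates *are* materially confounded, at close to the 2% design effect. Assumed correlations of 0.3 (BMI–metabolite) and 0.3–0.4 (BMI–birth weight) would give induced r = 0.09–0.12, R² = 0.8–1.4%, and p < 0.0001 about 15–46% of the time. But the document's 55 g implies a BMI–birth weight correlation of only about 0.11–0.14 under the SDs assumed above.
- A reader might conclude that baseline size belongs in every model. Where first-trimester weight is the exposure, adjusting for first-visit weight and height puts the exposure among its own covariates, and adjusting for first-visit BMI leaves a weight coefficient that mainly reflects height. For later weights, adjusting for first-visit weight changes the question from weight to gain.

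The defence does not remove the contradiction. An analysis plan can add a covariate, but it cannot supply prepregnancy data that the article says are lacking.

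**Conclusion.** The point holds for Objective 2 and the models in which metabolites are the exposure and offspring measures the outcome. The objective claims a property that the described data cannot deliver: prepregnancy BMI is lacking, no paternal measurement is described, and the governing confounder list holds no maternal size measure. Those estimates are open to confounding by early-pregnancy maternal size, along a path whose two links the article states itself.

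The size of the bias is not settled. On the article's 55 g per SD it is an induced R² of about 0.01–0.47%, given the assumed birth-weight SD and BMI–metabolite correlation. That is well under the 2% yardstick, and larger values need stronger assumed correlations. The 55 g is also a genetic estimate for prepregnancy BMI, so it is only a rough guide to the association with BMI at 10–13 weeks. Even if the bias proved small, the claimed independence would remain untested.

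**What to change.** - Reword Objective 2 so that independence is claimed from early-pregnancy (10–13 week) maternal BMI.
- Delete the paternal clause unless paternal data are actually recorded. If they are, state which measures and add them to the schedule and the model.
- In Data analyses, add first-visit BMI, derived from the height and weight already measured, to the confounder list for models in which metabolites (levels or changes) are the exposure and offspring measures the outcome.
- Do not add it to models in which trimester-specific maternal weight is itself the exposure.

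The cost is negligible: a change of wording and one covariate, with no new data collection. With R² = 2% read as a partial R², two-sided power at N = 1000 is 72.9% both with no covariates and with about eight. The claim becomes narrower, limited to BMI in early pregnancy, which already includes any weight change before the first visit.

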### Study area, design and setting

#### Study area

This study is being conducted in the government hospital of Sardar Patel Medical College, that is, 'Prince Bijay Singh Memorial Hospital' (PBM), located in the subdistrict *Bikaner*, which is one of the eight subdistricts ('*Tehsils')* of Bikaner district in Rajasthan state. According to Census of India,^59^ Rajasthan is India’s largest state in terms of geographical area, with a population size of 68 million. The population of Bikaner district is 2.3 million (66% is rural) of which 47% are females. In Bikaner, crude birth rate is 26 per 1000 individuals, the total fertility rate is 3 and the infant mortality rate is 60 per 1000 individuals.^60^ The majority of study participants are homemakers (80%), follow the Hindu religion (70%) and approximately 20% of the participants are illiterate. The choice of PBM hospital was based on the availability of government medical facility, which is the largest in district Bikaner and it ensures health care accessibility and affordability (due to free of cost treatment) for the entire population.

#### Study design

A hospital-based cohort study which is recruiting and longitudinally following the pregnant women until delivery, and their offspring at birth in district Bikaner, Rajasthan, India.

#### Sample size

Studies of fairly large size for detecting associations between longitudinal changes in levels of metabolites in pregnancy and fetal growth, and levels of metabolites of the offspring at birth, are few in number. For example, Ciborowski *et al*
61 used 770 samples collected during the first trimester for studying the relationship between maternal metabolic levels with macrosomia and low birth weight. Maitre *et al*
58 investigated 34 metabolites on 438 samples recruited during the first trimester and found an association with fetal growth restriction and preterm birth. The majority of studies related to metabolic changes during pregnancy^62–64^ and maternal-fetal medicine^65 66^ were based on 30–60 samples.^67 68^ Exact power calculations are challenging due to a restricted number of prior studies leading to unknown features.^69^ Even the largest study on 4212 participants for studying the predictive metabolomic biomarker for placental complications included limited sample of pre-eclampsia (n=134), fetal growth restriction (n=162) and controls (n=259).^17^ Thus, the proposed sample size must be larger than the majority of informative studies conducted to date and feasible within the cost boundaries for the technology being used.

Tynkkynen *et al*
70 studied quantitative urine and serum metabolite data on 995 samples of Northern Finland Birth Cohort for establishing the proof of concept for conducting large-scale epidemiological studies in metabolomics using an example of BMI. A relatively large study (n=800) has found that maternal urine metabolites can independently explain 12% of birth weight after adjusting for all other lifestyle/clinical factors.^16^ They also found an association of trimester-specific metabolic changes on fetal weight (change of 1.2% in first trimester and 2.4% in third trimester). Studies have observed that a metabolite level may change from 10% to 30% (even more for some metabolites) from first trimester to third trimester.^15 71^

For a cross-sectional analysis, a sample size of 1000 will be sufficient (with 98% power) to explain 4%–5% variation in the level of a metabolite by maternal weight as a predictor, even after correcting for multiple testing (α= 0.0001; for number of metabolites). Moreover, a sample size of 1000 will also be sufficient to explain 2% variation in the fetal growth parameters (with 80% power, α=0.0001) by maternal level of metabolite as a predictor.

Therefore, we propose to recruit 2500 pregnant women during the first trimester in order to measure metabolites on at least 1000 pregnant women (we may recruit >1000 women) in each trimester and their offspring, accounting for loss to follow-up.

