### Quantitative metabolomics

The quantitative data on the level of metabolites (in mothers during each trimester and in offspring using cord blood) will be generated through a targeted approach for screening the predefined and known metabolites using a commercial assay, that is, AbsoluteIDQ p400 HR kit (Biocrates Life Sciences, Innsbruck, Austria). It provides data on 400 endogenous metabolites from 11 metabolite classes (ie, amino acids, biogenic amines, monosaccharides, acylcarnitines, diglycerides, triglycerides, lysophosphatidylcholines, phosphatidylcholines, sphingomyelins, ceramides and cholesteryl esters). The choice of AbsoluteIDQ p400 HR kit based on proven utility of its previous version of kit (AbsoluteIDQ p180) in several metabolomics-based epidemiological studies.^9 95–98^ Our collaborator, the Phenome Centre Birmingham, University of Birmingham, UK, has experience of using this kit in an interlaboratory trial. For generating data on targeted metabolites, a triple quadrupole mass spectrometry-based technology will be used which characterises a metabolite by its molecular mass, its specific fractionation pattern (tandem mass spectrometry) and high sensitivity.^99^ The complete analytical process will be performed using the MetIQ software package, which is an integral part of these kits. The quality control procedure used by Suhre *et al*
100 will be followed for generation and cleaning of metabolomic data. One reference sample will be measured three times on each plate across the samples. The quality of metabolite data will be controlled by estimating their coefficient of variation and missing value rates.^15^ Outlying samples and data points will be excluded and finally all missing values will be imputed.^101^

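### On its printed inputs and a two-sided test, the fetal-growth calculation gives about 73% power for 2% explained variation, not the stated 80%

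*Protocol article*

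**What the plan says.** The Sample size section of the protocol article gives two power statements for 1000 women.

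- Metabolite level explained by maternal weight: "a sample size of 1000 will be sufficient (with 98% power) to explain 4%–5% variation in the level of a metabolite", described as holding "even after correcting for multiple testing (α= 0.0001; for number of metabolites".
- Fetal growth explained by a metabolite: "a sample size of 1000 will also be sufficient to explain 2% variation in the fetal growth parameters (with 80% power, α=0.0001", with one maternal metabolite as the predictor.

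Neither statement names the test, its sidedness or the software. The section also concedes that exact power calculations are difficult with so few earlier studies. Its closing paragraph plans to recruit 2500 women so that at least 1000 are measured. The 1000 is therefore the number analysed, and no further allowance for attrition applies.

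The alpha is tied to the number of metabolites. Of the assay, the Quantitative metabolomics section says: "It provides data on 400 endogenous metabolites from 11 metabolite classes". The Data analyses section plans regression models with false discovery rate correction.

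**The concern.** The second statement supplies everything needed to check it except sidedness: sample size, explained variation, alpha and a single predictor. Put through the usual regression test, those inputs do not return 80%.

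The statement is the only quantitative support in the article for the fetal-growth part of the second objective. If it is optimistic, a null result for a metabolite that truly explains 2% of the variation would be read against a 20% chance of missing it, when the printed inputs imply a larger one.

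**Working it through.** **Inputs** (Sample size section): n = 1000; R² = 0.02; one predictor; alpha = 0.0001. Sidedness is not given, so both are tried.

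**Effect size.** f² = R²/(1 − R²) = 0.02/0.98 = 0.02041. Noncentrality λ = n·f² = 1000 × 0.02041 = 20.41, and √λ = 4.518.

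**Hand check (normal approximation).** Power ≈ Φ(√λ − z).

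- Two-sided: z = 3.891, so Φ(4.518 − 3.891) = Φ(0.627) = 73.5%.
- One-sided: z = 3.719, so Φ(4.518 − 3.719) = Φ(0.799) = 78.8%.

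**Exact calculation.** Noncentral F with 1 and 998 degrees of freedom for the two-sided test (critical value 15.26), and noncentral t for the one-sided test.

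| Test | alpha | R² | Power |
|---|---|---|---|
| Two-sided | 0.0001 | 2% | 72.9% |
| One-sided | 0.0001 | 2% | 78.3% |
| Two-sided | 0.05/400 = 0.000125 | 2% | 74.7% |
| One-sided | 0.05/400 = 0.000125 | 2% | 80.0% |
| Two-sided | 0.0001 | 2.2% | 79.8% |

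At R² = 2% and alpha = 0.0001, other approximations (Fisher z, score z, alternative noncentrality definitions, seven covariates, a random predictor by simulation) give 71.4% to 73.5% two-sided and 77.4% to 78.8% one-sided. None reaches 80%.

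**What 80% two-sided requires.** With n = 1000 and alpha = 0.0001, R² = 2.21%. With R² = 2% and alpha = 0.0001, n = 1105. With n = 1000 and R² = 2%, alpha of about 0.00025.

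**Companion figure.** With n = 1000 and two-sided alpha = 0.0001, power is 99.4% at R² = 4% and 99.96% at R² = 5%. Both are above the stated 98%.

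**Which sidedness fits the study.** The effect is expressed as explained variation, which has no sign. The research questions ask only whether metabolic changes are associated with fetal growth. The assay screens about 400 metabolites with no stated direction for any of them. All of this points to a two-sided test.

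**The case against.** The strongest defence is that R² and alpha are printed to one significant figure and sidedness is not printed at all. A one-sided test at 0.05/400, which rounds to 0.0001, gives 80.0%. A two-sided test at R² = 2.2%, which rounds to 2%, gives 79.8%. The authors may therefore have calculated correctly and rounded. This stands as an explanation of how 80% could have arisen, and it means a calculation error is not proven. It does not rescue the sentence as printed: one route needs an unstated one-sided test together with a different alpha, and the other needs a different R². A reader given 2% and 0.0001 cannot recover 80% either way.

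It is also fair to say that little turns on the gap. The 1000 is a minimum, and the article allows for more. The planned false discovery rate correction is generally less strict than a fixed 0.0001, so 73% is not exactly the power of the planned analysis. The sample size is also justified by comparison with earlier studies and by cost. These points stand and limit the severity.

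A reader might infer that the 98% figure is wrong as well, since it does not match the computed 99.4% to 99.96%. The article claims only that 1000 is "sufficient (with 98% power) to explain 4%–5% variation in the level of a metabolite", and power above 98% confirms that. A reader might also object that the calculations do not cover weight gain, longitudinal change or mediation. The article introduces them as cross-sectional, and trimester-specific cross-sectional regressions are among the planned analyses, so that is not an error in these figures.

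**Conclusion.** The 80% does not follow from the printed inputs under a two-sided test. Power is 72.9%, about 7 points lower, and the type II error is 27% instead of 20%. Under a one-sided test at the printed alpha the shortfall is under 2 points (78.3%).

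The conclusion assumes a two-sided test, R² of exactly 2%, alpha of exactly 0.0001 and 1000 women analysed. The two-sided assumption is inferred from the study's undirected questions and is not stated in the article. The documents do not support the stronger reading that the study is underpowered or its sample size unsound: the gap closes at R² of about 2.2%, or with 105 more women analysed (1105 − 1000), and the 98% statement is conservative. Severity is minor to moderate.

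**What to change.** Replace the fetal-growth power statement with: *With n = 1000 and two-sided alpha = 0.0001, power is about 73% for R² = 2% and 80% for R² = 2.2%.* If the authors used a one-sided test or unrounded inputs, they should state these instead, so that the figure can be reproduced. Leave the 98% statement as it is.

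The cost is one sentence. Enrolment, objectives and analyses do not change.
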